#### Eligibility criteria

The suitability and feasibility of eligibility criteria will be determined by reviewing reasons for exclusion documented in the Approach/Screening Log and Screening and Post-Screening Case Report Forms, and reviewing characteristics of recruited patient participants documented in the Screening and Post-Screening Case Report Forms

#### Willingness/ability of physiotherapists

The willingness or ability of physiotherapists to recruit will be measured by subtracting the number of patient participants screened and approached from the number of admissions documented on the Approach/Screening Log

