The implementation of Early Supported Discharge has caused a change in patient caseload nationally for Stroke Rehabilitation Units [54] resulting in the majority of people admitted to Stroke Rehabilitation Units having complex needs and severe deficits. This change in caseload necessitates the design and evaluation of interventions for patients in Stroke Rehabilitation Units that target people with more severe deficits. The most common physical deficit caused by stroke is motor impairment, seen in approximately 80% of people [70]. It is the single most disabling factor in terms of limiting a person’s mobility, their ability to participate in activities of daily living (ADL) and to live independently [67]. Mobility encompasses a wide range of activities necessary for daily functioning: moving in bed, getting in/out of bed, on/off toilet, sitting out of bed, standing and walking [34]. These activities are particularly affected in the 15.5% of people with severe stroke [54] who require the assistance of two people to undertake ADL, may need equipment to aid transfers and are unable to sit unsupported, stand or walk [27]. They typically spend much of their time in bed and are dependent on a wheelchair/specialist seating when they sit out of bed [57].

Although immobility post-stroke is primarily caused by neurological damage, it can be exacerbated by other factors such as muscle wasting [56], reduced muscle length, increased muscle stiffness [47], joint contracture [26] and orthostatic hypotension. Orthostatic Hypotension (OH) is a sudden drop in blood pressure when moving from lying to standing, leading to symptoms of feeling faint, generalised weakness, cognitive slowing, and gradual or sudden loss of consciousness [38] and can, therefore, limit standing time. It can affect over 50% of people post-stroke [37] and should be addressed using non-pharmacological or pharmacological interventions, or a combination of the two [49, 64]. Secondary changes in the musculoskeletal and cardiorespiratory systems can theoretically be prevented or minimised by early mobilisation [65] especially standing [46]; prevention of these secondary changes underpins the rationale for the current trial.

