#### Willingness of patients to be randomised

The willingness of patient participants to be randomised will be measured by the recruitment rate, and number of participants who refused as documented on the Approach/Screening Log

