### Recruitment

Identification and recruitment will be by a healthcare professional on admission to one of four inpatient Stroke Rehabilitation Unit participating in the trial. This will be supported by the local NIHR Clinical Research Network. The healthcare professionals will log all admissions and screen patients for their stroke severity. All patients classified as a severe stroke will be screened for their eligibility, and any eligible participants will be approached within 48 h of the participant being deemed medically fit for rehabilitation or as soon as practicable.

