**Table Taba:** 

Feasibility indicator	Outcome measures	Data collection method
Process		
Recruitment rate	% of participants recruited/time	Case Report Forms
Retention rate	% of participants completed T1, T2, T3, T4, T5	Case Report Forms & Withdrawal Forms
Ability to consent	% of participants consenting	Screening/Approach Logs
Consent rate	% of consultee declarations	Case Report Forms
Eligibility criteria	% of admissions screened & eligible	Screening/Approach Log, Recruitment rate, Interview & Focus Group
Willingness of physiotherapists to recruit	% of admissions screened & approached	Recruitment rate, Interview & Focus Group
Willingness of patients to be randomised	% of participants who refuse to enrol in the trial	Recruitment Rate, Interviews & Focus Group
Acceptability of the intervention	% of withdrawals	Case Report Forms & Interview
Determining usual physiotherapy	Frequency specific physiotherapy interventions are implemented	Case Report Forms
Resources		
Burden	% of participants refusing physiotherapy sessions and follow-up assessments	Case Report Forms & Interviews & focus group
Cost effectiveness	*n* = duration (minutes) of functional standing frame programme session	Case Report Forms & Interviews
Management		
Fidelity	Observe intervention and control group sessions	Fidelity Checklists
Participant adherence	*n* = sessions per week	Case Report Forms
	*n* = minutes in standing	Case Report Forms & interview
	*n* = sit to stand repetitions	Case Report Forms & interview
	*n* = Yes; *n* = No for enjoyment	Case Report Forms & interview
	Score out of 10 for effort	Case Report Forms & interview
	Score out of 10 for fatigue	Case Report Forms & interview
Orthostatic hypotension protocol	% incidence of orthostatic hypotension	Case Report Forms
	% of incomplete sessions due to orthostatic hypotension (OH)	Case Report Forms
Safety		
Intervention	*n* = AE & SAE	Adverse Event and Serious
Data collection	*n* = AE & SAE	Adverse Event Forms

T1: baseline; T2: post-intervention period; T3: 3 months; T4: 6 months; T5: 12 monthsB)Clinical outcome measures

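### Physiotherapists' willingness to recruit is scored against all admissions, so non-severe and ineligible patients count against staff, and the text and table define it differently

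*Protocol article*

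**What the plan says.** Under Objectives, Process, the entry on willingness/ability of physiotherapists says that the indicator is "measured by subtracting the number of patient participants screened and approached from the number of admissions documented on the Approach/Screening Log". This is a raw count, higher is worse, and the source is the Approach/Screening Log.

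The feasibility outcomes table in the data collection section gives the same indicator as a percentage "of admissions screened & approached". Here higher is better. The data sources listed for the row are the recruitment rate, interview and focus group; the log is not among them.

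The Recruitment section fixes who is on the log and who should be approached. On logging: "The healthcare professionals will log all admissions and screen patients for their stroke severity". On approach: "All patients classified as a severe stroke will be screened for their eligibility, and any eligible participants will be approached".

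The entry on patients' willingness to be randomised says that "willingness of patient participants to be randomised will be measured by the recruitment rate". The sentence then adds the number who refused, taken from the log. The table row for this indicator is a refusal percentage.

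**The concern.** An indicator of staff willingness or ability should respond to what staff do with patients they could recruit. Here the base is everyone admitted. A unit that approaches every eligible patient will still show a large shortfall if many of its admissions are not severe or fail an eligibility criterion. The raw difference also grows with the size of the unit, so the four Stroke Rehabilitation Units cannot be compared on it.

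This matters for the use of the results. The section on progression to the full trial looks for at least 70% of the intended 50 participants (0.70 × 50 = 35) within 13 months, or solutions to any problems. If recruitment falls short, the Trial Steering Committee needs to know whether eligible patients were not approached, few were eligible, or patients refused. The stated indicator mixes the first two. The acceptability objective also draws on all the Process points, so the same figure carries over there.

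**Working it through.** The article gives no numerical value for this indicator, so there is no figure to reproduce. The check is a decomposition, then an illustration under assumed rates.

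**Decomposition.** Read naturally, a patient who was screened and approached is one to whom both happened. Following the Recruitment section:

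admissions − approached = non-severe + severe but ineligible + eligible but not approached

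Only the last term reflects willingness or ability. The table's percentage is approached / admissions, and its ceiling is eligible / admissions even when staff miss nobody.

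**Inputs.** The article gives no admission count, no severe fraction for the units and no eligible fraction. The Background says only that the shift in caseload left "the majority of people admitted to Stroke Rehabilitation Units having complex needs and severe deficits". All rates below are assumptions.

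**Every eligible patient approached, 300 admissions:**

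- 60% severe, half of those eligible: severe 300 × 0.60 = 180; eligible 180 × 0.50 = 90. Difference 300 − 90 = 210 (70%), made up of 120 non-severe and 90 ineligible. Table percentage 90 / 300 = 30%. Eligible patients missed: 0.
- 80% severe, 60% of those eligible: severe 300 × 0.80 = 240; eligible 240 × 0.60 = 144. Difference 300 − 144 = 156 (52%), made up of 60 non-severe and 96 ineligible. Table percentage 144 / 300 = 48%. Eligible patients missed: 0.

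**Wider range, 200 admissions, every eligible patient approached.** With 50% severe and 30% of those eligible, 200 − (200 × 0.5 × 0.3) = 170. With 90% severe and 70% eligible, 200 − (200 × 0.9 × 0.7) = 74. Fully willing staff thus score anywhere from 74 to 170 of 200 on the difference, and from 63% (126 / 200) down to 15% (30 / 200) on the table's percentage. Approached / eligible is 100% throughout.

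**Same score, different conduct.** Suppose the second 300-admission unit approached only 90 of its 144 eligible patients. Its difference is 300 − 90 = 210 and its table percentage 30%, identical to the first unit. Yet it missed 144 − 90 = 54 eligible patients (approached / eligible = 62.5%), while the first missed none.

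**Other readings of screened.** If the word alone meant screened for eligibility, ineligible severe patients would drop out of the difference, but all non-severe admissions would remain: 120 and 60 of 300 in the two scenarios. If it meant the severity screen applied to admissions, the difference would isolate patients whom staff failed to screen, but then approached would have no role.

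**Patient willingness.** The recruitment-rate objective defines that rate as participants recruited per month. That is the product of admissions per month and the severe, eligible, approached and accepting fractions. Only the last is patient willingness. The refusal measures do bear on it, but the text gives a count without a denominator, and the table's percentage is of participants, whereas someone who refuses to enrol never becomes one.

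**The case against.** The strongest reply is that little is lost. All admissions are logged, and the eligibility-criteria objective plans "reviewing reasons for exclusion documented in the Approach/Screening Log", so eligible patients could be counted and the right denominator rebuilt. The indicator does not stand alone either: eight physiotherapist interviews and a focus group covering participant recruitment are planned, and physiotherapists' views on whether a later trial is achievable are an explicit qualitative objective. It is descriptive, no hypothesis is tested, and it is not among the listed progression criteria. All of this stands. It limits the harm, but the definition as written would still be computed from the wrong base.

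Three stronger readings are tempting and are not supported:

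- A reader might infer that the objective cannot be answered at all. The logged exclusion reasons and the qualitative work show otherwise. The failure is confined to the stated quantitative measure.
- A reader might apply the 15.5% severe-stroke figure from the Background to unit admissions and, with half eligible, obtain 300 − 23 = 277 (92%). The article does not give 15.5% as the case mix of these units. It says that most people admitted to them have severe deficits, and that mild and moderate strokes are routed to Early Supported Discharge.
- A reader might conclude that patient willingness rests on the recruitment rate alone. Refusals are already in both the text and the table, so only a poor companion measure and an unsuitable denominator remain.

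**Conclusion.** The point holds for the stated quantitative measure. Under the article's own recruitment flow, both definitions count non-severe and ineligible admissions against staff, and they disagree on form (difference or percentage) and on data source. In the two 300-admission illustrations, 70% and 52% of admissions count as not approached although no eligible patient was missed. Those sizes depend wholly on assumed severity and eligibility rates; the direction does not, provided that some admissions are non-severe or ineligible. The conclusion rests on the natural reading that screened and approached means both. It should be corrected, but it does not endanger the feasibility trial. The patient-willingness point is secondary.

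**What to change.** In the physiotherapist-willingness objective and its table row, use one definition: eligible patients approached / eligible patients, by unit, with the Approach/Screening Log as the source and the interviews and focus group kept as support.

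Report screening completeness separately, by unit, as two proportions: admissions screened for severity / admissions, and severe strokes screened for eligibility / severe strokes.

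For patient willingness, in both the objective and the table, report refusals / eligible patients approached, and do not use recruitment per month as a measure of willingness. It stays as the recruitment-rate indicator in its own right.

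The cost is re-worded definitions in two objectives and two table rows. As the article describes it, the log already covers admissions, exclusion reasons, approaches and refusals, so no new collection should be needed. The one thing to confirm is that the severity result is held for each logged admission, since the log itself is not shown.

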#### Willingness of patients to be randomised

The willingness of patient participants to be randomised will be measured by the recruitment rate, and number of participants who refused as documented on the Approach/Screening Log

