## Aims

The *primary aim* of this trial is to establish whether a RCT of a functional standing frame programme in people with severe stroke in an inpatient sub-acute stroke rehabilitation setting is feasible.

The *secondary aim* is to explore the experience of this functional standing frame programme on the individual’s daily life, as well as the experience of being recruited and randomised to the trial, from the perspective of both the person with stroke and their relative/carer, using qualitative methods.

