### Process

#### Recruitment rate

The recruitment rate will be defined as the number of participants recruited per month. This information was recorded in the study log at each site.

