#### Consent rate

The consent rate will be calculated by dividing the number of individuals who met inclusion criteria, by the number who consented to participate in the trial. Reasons why eligible individuals are not interested in participating will be recorded by the PI/recruiting therapist in the approach/screening log.

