### Qualitative evaluation

Qualitative methodology will enable exploration of the thoughts, feelings and experiences of trial participants, their relatives and treating physiotherapists/PIs. Stratified purposive sampling will be used to achieve maximum variation to request semi-structured interviews with 16 participants (approximately six in the functional standing frame group, six in the usual physiotherapy group and four people who decline to participate or withdraw), eight relatives and eight treating physiotherapists. A combination of face-to-face, telephone or Skype will be offered for the interviews to inform the most appropriate method for the definitive main trial. The aim of the qualitative interviews is to address several uncertainties or unknowns including recruitment, retention, practical implementation of the intervention, acceptability/tolerance of the intervention, informed consent, and suitability and acceptability of outcomes measures to inform the design and implementation of the definitive main trial.

People with mild to moderate aphasia will be interviewed as it is important to seek the perspectives and experiences of people with aphasia due to its high prevalence in people with stroke. However, people with severe aphasia (unable to complete the patient-report outcome measures) will be unable to participate due to inability to comprehend and/or express their views and will therefore be excluded.

All physiotherapists involved in delivering the trial (PIs and treating physiotherapists) will be invited to a focus group at the end of the recruitment period to discuss their experiences of delivering the trial (participant recruitment, documentation, delivery of the intervention, etc.) to further evaluate and improve procedures for the definite trial. All interviews and focus group will be digitally recorded and transcribed verbatim.

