### Determining progression to the full trial

Progression to a full trial application will occur if minimum success criteria are achieved in key feasibility aims and objectives, and/or if solutions can be identified to overcome any issues. These criteria will be finalised in discussion with the Trial Steering Committee, but are likely to include a minimum of:70% recruitment of the intended 50 patient participants within the 13-month recruitment window80% of consented patient participants randomised to the intervention group engaging with and adhering to a minimum of five session per week during the three-week SPIRES intervention80% completion rate of outcome measures (including follow-up)

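### The quantitative measure of patients' willingness to be randomised does not separate it from patient flow or from other reasons for declining

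*Protocol article*

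**What the plan says.** Patients' willingness to be randomised is a named feasibility objective (Abstract, Methods/design). Its definition, in the subsection of that name under Process, reads: "The willingness of patient participants to be randomised will be measured by the recruitment rate, and number of participants who refused as documented". The refusals are those entered in the approach/screening log. The first component is defined under Recruitment rate: "The recruitment rate will be defined as the number of participants recruited per month".

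The feasibility outcomes table gives this indicator as the percentage "of participants who refuse to enrol in the trial", without stating the denominator. It lists the data sources as "Recruitment Rate, Interviews & Focus Group".

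Three other places bear on the point:

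- Under Consent rate: "Reasons why eligible individuals are not interested in participating will be recorded by the PI/recruiting therapist in the approach/screening log".
- The secondary aim covers the "experience of being recruited and randomised to the trial", from the viewpoint of the patient and of the relative or carer.
- Qualitative evaluation plans 16 patient interviews: about six per arm and "four people who decline to participate or withdraw".

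**The concern.** A measure of willingness to be randomised should change when willingness changes and stay put when it does not. Neither component does this.

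Recruits per month has no denominator of eligible or approached people. It rises and falls with the number of severe strokes admitted, with the exclusion list, and with whom staff approach. The table also names the recruitment rate as a source for the eligibility criteria and for physiotherapists' willingness to recruit. One number cannot tell these three explanations apart.

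The refusal count takes every refusal alike. The Discussion itself names barriers unrelated to allocation by chance, such as fatigue, poor exercise tolerance, communication difficulty and being overwhelmed. Entry through a consultee is allowed, but refusals are not split by who decided. Randomisation follows consent and all baseline assessments, and anyone who leaves in that gap is outside this measure.

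At stake is the reading of one objective. The reported figure could be taken as evidence about randomisation when it reflects patient flow or general reluctance to join.

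**Working it through.** The protocol gives no target or expected value for this indicator, so there is no figure to reproduce. The check asks whether the two stated numbers determine the quantity of interest.

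**Inputs from the protocol.** 50 participants and a 13-month window (Determining progression to the full trial: "70% recruitment of the intended 50 patient participants within the 13-month recruitment window"). **Assumed inputs.** Numbers approached, agreement proportions and reasons for refusal.

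**Step 1: same recruitment rate, different willingness.** Recruits per month = (eligible people approached per month) × (proportion agreeing). The full target is 50/13 = 3.85 per month. Approached per month is 3.85 divided by the agreement proportion. Total refusals are 50 divided by that proportion, minus 50.

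| Assumed agreement | Approached per month | Refusals in total |
|---|---|---|
| 90% | 4.27 | 5.6 |
| 70% | 5.49 | 21.4 |
| 50% | 7.69 | 50.0 |
| 40% | 9.62 | 75.0 |

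An identical recruitment rate is compatible with agreement from 90% down to 40%.

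**Step 2: same willingness, different flow.** Fix agreement at 70%. Recruits per month = 0.7 × approached; refusals = 0.3 × approached × 13.

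| Assumed approached per month | Recruits per month | Refusals in 13 months |
|---|---|---|
| 3 | 2.1 | 11.7 |
| 5 | 3.5 | 19.5 |
| 8 | 5.6 | 31.2 |

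Both stated components more than double while willingness does not change.

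**Step 3: both components together.** Assume 50 recruited and 30 refusals, so 80 approached and 50/80 = 62.5% agreeing. Let s be the share of refusals due to randomisation. The proportion not objecting to randomisation is 1 − 30s/80.

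- s = 0: 100%
- s = 0.5: 1 − 15/80 = 81.25%
- s = 1: 1 − 30/80 = 62.5%

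With a proper denominator, the refusal percentage (37.5%) gives only an upper bound on refusal because of randomisation. The missing quantity is s, which comes from the reasons for refusal.

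**Step 4: where the reasons are.** They are recorded in the same log that supplies the refusal count, but the text places them under Consent rate. Neither the definition of this indicator nor its table row says they will be used for it, and the table row does not list the log as a source.

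**The case against.** The strongest reply is that the trial collects what is needed and looks at the question in other ways. Reasons for declining are logged. The table adds interviews and a focus group to this indicator. The experience of randomisation is part of the secondary aim and a separate qualitative objective, and some decliners are to be interviewed. Admissions, screening and approach are reported under neighbouring indicators, so patient flow can be seen alongside. Withdrawals are counted under acceptability of the intervention, with reasons on a standard form. Consents and consultee declarations are counted separately.

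Most of this stands, and it limits the point to the quantitative definition. A reader might infer that the trial as a whole cannot show whether randomisation is acceptable. The documents do not support that, because the logged reasons and the interviews can inform it. A reader might also link this indicator to the stepped-wedge design mentioned under Control (usual physiotherapy). That option is raised because the same therapists are expected to deliver both arms, not because patients may refuse randomisation. Nor does the protocol say that a slow month will be read as unwillingness.

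The reply does not repair the definition. About four interviews, shared between decliners and withdrawers, can explain reasons but cannot estimate a proportion. People with severe aphasia are not interviewed. The focus group consists of physiotherapists, so it is indirect evidence about patients. Exploring the experience of being randomised does not reach people who refused to be. How reasons are coded could be left to the forms or the analysis plan, but the article has already fixed a measure, and that measure captures something else.

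**Conclusion.** The point holds for the quantitative measure: recruits per month and total refusals do not identify willingness to be randomised. In the illustration, one recruitment rate fits agreement anywhere from 40% to 90%, and adding the refusal count still leaves the share not objecting to randomisation between 62.5% and 100%. These ranges rest on assumed approach and refusal numbers; the 50 and the 13 months are the protocol's. The illustration also assumes that each refusal can be assigned to one main reason.

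The point is minor. The likely progression criteria concern recruitment against target, adherence and completion of outcome measures, not this indicator, and no sample size depends on it.

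**What to change.** Reword the definition under Willingness of patients to be randomised and the matching table row:

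- Remove the recruitment rate from this indicator. It remains an indicator in its own right.
- Report the number of eligible, approached people whose logged reason for declining is randomisation or a preference for one arm, divided by all eligible people approached. Show decisions by patients and by consultees separately.
- Add the number of consented participants who withdraw before randomisation or who give their allocation as the reason for withdrawing, by arm where allocated.
- Name the approach/screening log and the withdrawal forms as sources, and read both figures with the interview data.

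The cost is a reason code on the existing log and the rewording; no extra visits or staff are needed. The counts will be small: with 80 people approached, as assumed above, one person moves the proportion by 1/80 = 1.25 percentage points. The result should therefore be given as counts with their denominators and described as such. The analysis plan is still to be written according to Data analysis, so the definition can be carried into it.
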